### Setting

Patients will be recruited between November 2014 and August 2016. The study will be performed in four vocational rehabilitation centers in the Netherlands that are part of a nationwide network of twelve VR centers. The four participating centers in this study are geographically spread across the Netherlands and have been selected according to the number of patients expected to be referred in 2014 to 2016.

### Recruitment of participants

Recruitment of participants occurs in five steps; the first three steps are regular steps and the last two steps have been added especially for this study. Step 1. Patients will be referred to one of the four participating centers by either an occupational physician, medical specialist, general practitioner, or employer. Step 2. A rehabilitation physician (RP) will assess the patient’s medical history, bio-psychosocial restrictions, and work-related limitations. Step 3. A multidisciplinary screening comprising a mental, physical and occupational assessment will take place, which will be performed by a psychologist, physiotherapist, and occupational specialist. Step 4. After completing the multidisciplinary screening, the patient will be provided with verbal and written information about the study. When all study criteria have been met, which will be decided by the RP, the patient will be asked to sign the informed consent form. Step 5. When the patient has granted written informed consent, the patient will be randomized into 40-h or 100-h vocational rehabilitation.

### Interventions

#### 40-hour vocational rehabilitation

The 40-h vocational rehabilitation is a multidisciplinary bio-psychosocial [29] group-based program and consists of work participation coordination (10 h), and a choice of 30 h of a set of modules offered in the 100-h vocational rehabilitation program, such as graded activity, cognitive behavioral therapy, group education, and relaxation. These modules are described in detail in Appendix 1. Since the choice of 30 h of modules will be prioritized by the multidisciplinary screening team after the multidisciplinary screening at baseline, the content may differ among patients. The 40-h VR lasts a maximum of 40 h in 15 weeks. Each rehabilitation center will prioritize the number of sessions per participant per week, but the following framework will be a guideline for the rehabilitation centers: weeks 1-5 two sessions/week, weeks 6-10 one session/week, weeks 11-15 2-3 sessions in five weeks. The 40-h VR program will be extended in case of the following: a patient’s percentage of working hours per week pertaining to contract hours at discharge compared with working hours per week pertaining to contract hours at baseline is extended by 25 to 50 %, and the multidisciplinary team expresses strong arguments that the patient is likely to benefit from the extension. However, this protocol deviation should occur in no more than 5 % of the cases. This percentage is arbitrarily chosen by the authors of this paper; if more than 5 % of the participants deviate from the study protocol, the robustness on non-inferiority (that is, research question 1) will decline [30].

#### 100-hour vocational rehabilitation

The 100-h vocational rehabilitation is a multidisciplinary bio-psychosocial group-based program and encompasses a set of modules: work participation coordination, graded activity, cognitive behavioral therapy, group education, and relaxation. These modules are described in detail in Appendix 1. The 100-h VR consists of approximately 100 h and is an existing VR program in the Netherlands conducted by 12 rehabilitation centers, four of which will participate in this study. The 100-h VR is delivered over a period of 15 weeks with two sessions (approximately 3.5 h/session) per week. The 100-h VR appears similar to other VR trials [17, 31] but has a longer duration (in weeks) and consists of more graded activity hours compared to similar studies [18, 21, 32].

### Data collection

Self-reported data will be collected using web-based questionnaires. Data will be collected at baseline (that is, before and during the multidisciplinary screening, T0), 7 weeks after the start of the intervention (midterm, T1), 14 weeks after the start of the intervention (discharge, T2), and at 2, 4, 6, 8, 10 and 12 months follow-up after discharge (T3-T8). Figure 2 shows the timing of the data collection. In addition, pilot data show an expected delay of approximately 1.5 months between baseline and the start of the intervention. At each data point, participants will receive an email with login data and the request to complete questionnaires on a website. If participants do not complete the questionnaire within a week, they will receive a reminder email. If the questionnaire is not completed after this reminder, patients will be telephoned by a researcher (TB), who will ask patients to complete the questionnaire. Table 1 presents the outcome measures of the data collection.

**Fig. 2 Fig2:**
[figure not shown]
Timing of data collection

**Table 1 Tab1:** Outcome measures for each of the measurement moments

Outcomes	Time measured			Follow-up					
	Baseline	Midterm	Discharge	2 months	4 months	6 months	8 months	10 months	12 months
	T0	T1	T2	T3	T4	T5	T6	T7	T8
Descriptive variables									
Demographic variables	x								
General perceived health	x								
Work-related psychosocial factors	x								
Self-efficacy of work participation	x								
Pain intensity	x		x						
Fatigue	x								
Work tolerance functions	x								
Outcome measures									
Primary									
Work participation^a^	x	x	x	x	x	x	x	x	x
Secondary									
Work ability	x		x			x			x
Disability	x		x			x			x
Physical functioning	x		x			x			x
Quality of life	x		x			x			x
Costs^a^									
Presenteeism	x	x	x	x	x	x	x	x	x
Health care usage	x		x		x		x		x

^a^The primary outcome *work participation* will also serve as a cost outcome (that is, absenteeism)

### Outcome measures

The selection process of the questionnaires used in this study and information about their validity and reliability is described in a core set paper [33]. Primary, secondary, and cost outcomes will be assessed to answer the research questions.

#### Primary outcome

The primary outcome in this study is work participation expressed as total sick leave days due to subacute or chronic musculoskeletal pain. Total sick leave days will be calculated from the start of the intervention until 12 months follow-up after discharge. Sick leave will be measured using the absenteeism items of the iMTA (institute for Medical Technology Assessment) Productivity Cost Questionnaire (iPCQ) [34]. The questionnaire has a recall period of 4 weeks and measures sick leave on working days and on a generic basis (that is, the reason for sick leave is not asked). We have made slight adaptations to measure sick leave specifically (that is, related to subacute or chronic musculoskeletal pain, or other reasons such as flu), and we have added an item to assess the working hours at this moment: “Are you working for the full number of hours you were contracted for?” This question has three possible answers: “yes,” “no, I am partly at work,” and “no, I am on 100 % sick leave.” After the answer “no, I am partly at work” the participant is asked to fill in the number of hours he/she is working per week at that moment. The iPCQ is the result of combining two existing Dutch questionnaires (PRODISQ and SF-HLQ), and is recommended by the Dutch guideline for health economic evaluations [35]. The iPCQ has been translated by a professional language institution into a patient-friendly version using more simple language, thereby increasing the feasibility and validity of the questionnaire [34]. A population with mental health problems showed a satisfactory reliability regarding the iPCQ absenteeism items (icc 0.83) [36]. Until now, reliability of the iPCQ has not been tested in our study population. This needs to be done in the near future.

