#### Secondary outcomes

Secondary outcomes include the following:Work ability will be measured using a single item of the Work Ability Index (WAI) [37]. The current work ability compared to lifetime best work ability can be scored on a 0 to 10 response scale, where 0 represents “completely unable to work” and 10 represents “work ability at its best”.Disability will be measured using the Pain Disability Index (PDI). The PDI is a 7-item questionnaire for investigating the magnitude of the self-reported pain-related disability, independent of region of pain or pain-related diagnosis. The PDI measures family/home responsibilities, recreation, social activity, occupation, sexual behavior, self-care, and life support activity. The questionnaire is constructed according to a 0 to 10 numeric rating scale in which 0 means no disability and 10 maximum disability. Total scores can range from 0 to 70, with higher scores reflecting higher interference of pain with daily activities [38, 39].Physical functioning will be measured using the physical functioning subscale of the RAND-36. The questionnaire assesses self-reported physical functioning independent of (pain) diagnosis [40]. The physical functioning scale consists of 10 questions with three possible answers: “yes, limited a lot,” “yes, limited a little,” and “no, not limited at all.” The total score can range from 0 to 100, with higher scores indicating better physical functioning. The validity and reliability of the Dutch version are good [41].Quality of life will be measured using the validated Dutch version of the EuroQol-5D (EQ-5D) [42, 43]. The EQ-5D measures five dimensions: mobility, self-care, activities of daily life, pain and anxiety/depression on a categorical scale (1 to 3). The EQ-5D is a widely employed instrument used to assess health-related quality of life (QoL), and is recommended by the Dutch guideline for health economic evaluations [35]. To allow comparison between several conditions and interventions, Quality Adjusted Life Years (QALYs) will be calculated in three steps. First, the EQ-5D scores (measured at baseline, discharge, 6-month follow-up, and 12-month follow-up) will be converted to utility scores using the Dutch EQ-5D tariff [43]. Second, QALYs will be calculated from three time periods (1 = baseline to discharge, 2 = discharge to the 6-month follow-up, 3 = 6-month follow-up to the 12-month follow-up). Third, one summated QALY will be calculated from the calculated QALYs in step two.

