### Non-inferiority hypothesis

A reduction in sick leave days of more than 30 days per year is deemed a clinically significant improvement on work participation [15, 17–19, 24]. A difference in sick leave days of 30 or fewer (from the start of the intervention until 12-months follow-up) between 40-h and 100-h VR is assigned as the margin of non-inferiority in this study. Our hypotheses are as follows:H0: μ1 - μ2 ≥30H1: μ1 - μ2 <30

H0 is the null hypothesis, and H1 is the alternative hypothesis, μ1 is the mean number of sick leave days in the 40-h VR group, and μ2 is the mean number of sick leave days in the 100-h VR group.

Non-inferiority is claimed if the upper bound of the one-sided 95 % confidence interval of the treatment effect difference (μ1 - μ2) on work participation does not exceed 30, which means that the risk of it being inferior is within acceptable boundaries [30]. We expect a normal distribution of the primary outcome work participation. If the data on the primary outcome does not follow a normal distribution, we will perform log transformations. The margin of non-inferiority will then be interpreted as a 28 % increase in the sick leave days’ difference of μ1 - μ2. We calculated this percentage as follows:$$ 30/107 = 28\ \% $$

where 30 denotes the margin of non-inferiority and 107 the expected mean days of sick leave in the 100-h VR arm [15, 17–19, 24] during the timing of the data collection, which equals approximately 15.5 months (intervention period of 3.5 months + the follow-up period of 12 months, see Fig. 2).

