### Randomization

An independent statistician prepared the randomization by using computer-generated randomization tables. To prevent unequal randomization, employees are pre-stratified by duration of sick leave (short-term <6 weeks or long-term ≥6 weeks) and whether they are on full-time (100 %) or part-time (≤99 %) sick leave. Block randomization with blocks of four will be applied to ensure equal group sizes within each stratum. A separate block randomization table is generated for each of the four participating vocational rehabilitation centers. For each stratum, the researcher will prepare opaque, sequentially numbered, and sealed coded envelopes, with a note for either the 40-h VR or 100-h VR. After the multidisciplinary screening (at baseline), the multidisciplinary screening team and rehabilitation physician will fulfil all study criteria. If participants meet all criteria, they will be allocated to 40-h or 100-h VR. Treatment allocation will be performed by a member of the multidisciplinary screening team (MST) at each center and can be performed at the center or via telephone (this will differ among the centers). The MST member hands over two envelopes (left over) of that stratum, and the patient is asked to pick one of the envelopes, open the envelope and sign the note. In the case of telephone allocation, the MST member will ask the patient to sign informed consent and to return it via a reply envelope. When the signed informed consent is received, the MST member will perform the treatment allocation without the patient. After randomization, a research assistant will make an appointment for the patient’s first intervention date.

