### Co-interventions and compliance

The patients’ self-reported healthcare usage data will be used for the assessment of co-interventions. Compliance will be assessed using information about attendance to the program and compliance to the treatment protocol and will be assessed after each intervention session in an electronic log by a member of the multidisciplinary intervention team (MIT). Furthermore, the MIT member will determine at discharge if the program was completed as planned. This will be assessed on a binary scale: “program completed as planned,” or “program deviated.” In the latter case, a closed question follows: program deviated due to “early discontinuation due to adverse events such as accident, surgery, or major private event,” “early discontinuation due to goals being achieved,” “extension of intervention program due to non-achievement of goals,” or “other reasons.” In the case of an early discontinuation or extension of the program, the number of deviated weeks will be reported. The information about compliance will be applied to perform the per protocol analyses.

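### QALYs accrue from baseline but sick leave days and absenteeism costs from the start of the intervention, about 1.5 months later; a randomised patient who never starts has no defined outcome window

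*Protocol article*

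**What the plan says.** All references are to the Protocol article.

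- **Sick leave days.** Section Primary outcome: "Total sick leave days will be calculated from the start of the intervention until 12 months follow-up after discharge". Section Non-inferiority hypothesis ties the 30-day margin to this window and gives its length: "which equals approximately 15.5 months (intervention period of 3.5 months + the follow-up period of 12 months, see Fig. 2".
- **Costs.** Section Cost outcomes takes absenteeism from the primary outcome data. The employer analysis uses the intervention period plus follow-up. Section Cost-utility analysis states no cost window.
- **QALYs.** Section Secondary outcomes: "QALYs will be calculated from three time periods (1 = baseline to discharge", followed by two further periods up to the 12-month follow-up.
- **Baseline.** Section Data collection: "Data will be collected at baseline (that is, before and during the multidisciplinary screening, T0". Randomisation comes after screening and consent. The same section adds that "pilot data show an expected delay of approximately 1.5 months between baseline and the start of the intervention".
- **Start of the intervention.** Section Randomization: "After randomization, a research assistant will make an appointment for the patient’s first intervention date". Section Blinding says that blinding is not possible, apart from the data analyst.
- **Discharge.** Section Data collection places the later questionnaires at "14 weeks after the start of the intervention (discharge, T2), and at 2, 4, 6, 8, 10 and 12 months follow-up after discharge (T3-T8", without distinction by arm. The programmes are described as running up to 15 weeks, with an extension foreseen for some patients in the 40-h arm. Section Co-interventions and compliance says: "In the case of an early discontinuation or extension of the program, the number of deviated weeks will be reported".
- **Analysis sets.** Section Statistical methods requires both the intention-to-treat and the per-protocol analysis to show non-inferiority.

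**The concern.** Two time origins are in use. QALYs begin before randomisation. Sick leave days, and the absenteeism costs built on them, begin at an event after randomisation. A cost-utility ratio should relate costs and health effects over the same period, and here it would not.

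The later origin raises a second question for the primary analysis. The first session is booked once allocation is known, and T1 to T8 are all timed from the start or from discharge. A patient who is randomised but never starts therefore has no time zero and no due date for any questionnaire after baseline, yet belongs in the intention-to-treat analysis. Omitting such patients would weaken that analysis. If one arm waited longer than the other, the two arms would also be observed over different stretches of time since randomisation, and the day count would move without any effect of treatment.

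**Working it through.** **1. The plan's own window.** Inputs: 3.5 months of intervention and 12 months of follow-up (section Non-inferiority hypothesis).
3.5 + 12 = 15.5 months, as stated. With T2 at 14 weeks and 4.348 weeks per month: 14/4.348 + 12 = 3.2 + 12 = 15.2 months, which still agrees with the plan's approximate figure.

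**2. The QALY window.** Add the 1.5-month delay (section Data collection).
15.5 + 1.5 = 17.0 months, or 15.2 + 1.5 = 16.7 months with T2 at 14 weeks.

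**3. The gap.** 1.5/17.0 = 8.8 % of the QALY window; 1.5/15.5 = 9.7 % of the sick-leave window.

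**4. What the gap holds per patient.**
- QALYs, assuming a utility of 0.5 to 0.7: 0.5 × 1.5/12 = 0.06 to 0.7 × 1.5/12 = 0.09.
- Working days, for a five-day week: 1.5 × 4.348 × 5 = about 33 on full sick leave, about 16 on half-time leave.

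These are amounts per patient, not differences between arms. With equal waits they largely cancel in expectation.

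**5. Weight of baseline utility in the QALY difference.** By the trapezium rule, T0 carries half of the baseline-to-discharge period: (6.5 + 14)/2/52 = 0.197 years. An assumed chance imbalance of 0.05 in T0 utility then adds 0.197 × 0.05 = 0.010 QALY if unadjusted. Starting the QALY at the intervention and carrying T0 utility forward would still give 7/52 × 0.05 = 0.007, so this is mainly a reason to adjust for T0 utility.

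**6. Sensitivity of the day count to unequal waiting.** Planned mean rate: 107/15.5 = 6.9 days per month; 6.9/4.348 = 1.6 days per week. The ceiling for a five-day worker is 5 days per week.

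| Assumed difference in wait | At mean rate | Ceiling | Ceiling as share of the 30-day margin |
|---|---|---|---|
| 1 week | 1.6 days | 5 days | 17 % |
| 2 weeks | 3.2 days | 10 days | 33 % |
| 4 weeks | 6.4 days | 20 days | 67 % |

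A shifted window loses an early week and gains a late one, so the true effect is the difference between the two weekly rates. With 3 to 4 days early and 1 day late (assumption) it is 2 to 3 days per week of difference in wait. It is smaller to the extent that recovery follows the start of treatment rather than calendar time. The documents give no wait by arm, so the table shows sensitivity and does not estimate a bias.

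**The case against.** **Unequal window length.** A reader might infer that the arms are followed for different lengths of time because the 40-h programme can be extended or end early. The documents do not support this. T2 is set at 14 weeks after the start in both arms, one window of about 15.5 months is given, the 15-week maximum applies to both programmes, and early discontinuation is not specific to an arm. If discharge did mean the actual end of the programme, extension in 5 % of the 40-h arm by 4 weeks on average (assumption) would add 0.05 × 4 = 0.2 weeks, about 0.3 days at the mean rate, or 1 % of the margin. What stands is that the 14-week discharge point and the 15-week or extended programme do not match.

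**Waiting time.** A reader might also take the 1.5 months as the wait after randomisation. It runs from baseline, so the wait after randomisation is shorter and is not given. Nothing suggests that it differs by arm.

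**Non-starters.** Intention-to-treat and multiple imputation are both specified, no section drops non-starters, and an analysis plan may hold a dating rule. That is fair. The article nevertheless fixes an anchor that such a patient does not have, and imputation needs a defined window.

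**No questionnaire at the start.** Section Effectiveness covers this by linear extrapolation across T0 to T8.

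**Cost window.** The cost-utility section states none, and absenteeism, presenteeism and healthcare use are all collected at T0, so costs could be accrued from baseline. This stands as a caveat. It also shows that the repair needs no new data.

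**Conclusion.** The mismatch in time origin holds. As written, QALYs cover about 17 months, while sick leave days and the absenteeism costs derived from them cover about 15.5, a difference of about 1.5 months or 9 to 10 %. This rests on the pilot delay and on reading the absenteeism costs as following the primary outcome window. The effect on the incremental ratio is probably modest, because the extra period largely cancels if waits are equal.

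The start-based time zero leaves the intention-to-treat outcome undefined for non-starters and makes the day count sensitive to unequal waiting, at about 1.6 days per week of difference at the planned mean rate. No such difference is documented, so this is an exposure and not a demonstrated bias.

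It may be tempting to conclude that the primary window should be replaced by a fixed period from randomisation, such as the 66 weeks (14 + 52) from start to T8. The documents do not support going that far. The 30-day margin and the 107-day mean were set for the start-based window. With a wait near 6.5 weeks, 66 weeks from randomisation would end 66 − 6.5 − 14 = 45.5 weeks after T2, short of 12 months. Exchanging treated for untreated time would also tend to pull a true difference towards zero, which favours a non-inferiority claim.

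**What to change.** 1. In the cost-utility analysis, accrue all costs and QALYs over one common period from baseline to T8, and say so in that section. Absenteeism, presenteeism and healthcare use are already collected at T0.
2. Adjust the between-arm QALY difference for T0 utility.
3. Keep the start-of-intervention window for the primary outcome. Retain non-starters by taking the planned first appointment as their time zero. Where no appointment was made, a nominal date such as 1.5 months after baseline, the plan's own expected delay, would serve.
4. Add a sensitivity analysis of sick leave days counted from baseline or randomisation, with all randomised patients.
5. Reconcile the 14-week discharge point with the 15-week or extended programme, and state whether discharge means the scheduled T2 or the actual end of the programme.

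The cost is wording and some extra derivation; sample size and questionnaires do not change. The downside is that the waiting period rests on extrapolation from T0 to T1, and for healthcare use from T0 to T2, since Table 1 does not list it at T1.

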### Statistical methods

All statistical analyses will be performed at the patient level, with descriptive statistics being used to compare the baseline measurements of the two intervention groups. If necessary, analyses will be adjusted for baseline differences. All analysis will be performed according to the intension-to-treat principle and the per protocol principle [30, 54]. To claim non-inferiority, both intention-to-treat and per protocol analysis must show non-inferiority [54]. Missing data on costs and effects will be assessed using multiple imputation techniques [25]. The imputation technique will depend on the results (that is, missing completely at random, missing at random, or missing not at random).

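### The primary sick-leave window and the T1–T8 dates start at a post-randomisation event, so a randomised patient who never starts has no defined window and any arm difference in waiting would enter the non-inferiority test

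*Protocol article*

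**What the plan says.** All references are to the protocol article.

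- **Outcome window** (Primary outcome): "Total sick leave days will be calculated from the start of the intervention until 12 months follow-up after discharge". The sections Non-inferiority hypothesis and Effectiveness use the same starting point.
- **Questionnaires** (Data collection): for baseline, "Data will be collected at baseline (that is, before and during the multidisciplinary screening, T0"; then "7 weeks after the start of the intervention (midterm, T1), 14 weeks after the start of the intervention (discharge, T2"; then "at 2, 4, 6, 8, 10 and 12 months follow-up after discharge (T3-T8".
- **Wait** (Data collection): "pilot data show an expected delay of approximately 1.5 months between baseline and the start of the intervention".
- **Order of events** (Recruitment of participants; Randomization): screening, written consent, allocation, and then booking: "After randomization, a research assistant will make an appointment for the" patient to begin. The Blinding section states that patients and teams cannot be blinded.
- **Analysis sets** (Statistical methods): "All analysis will be performed according to the intension-to-treat principle and the per protocol principle". Both must show non-inferiority before it is claimed. Multiple imputation is planned for missing costs and effects.
- **QALYs** (Secondary outcomes): "QALYs will be calculated from three time periods (1 = baseline to discharge", followed by two six-month periods after discharge). Absenteeism cost is taken from the primary outcome data (Cost outcomes).

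**The concern.** Intention-to-treat compares everyone randomised over a period whose beginning does not depend on what happened after allocation. Here the beginning is the first treatment session, which falls after patient and team know the arm. Three things follow.

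1. A patient who recovers, withdraws or declines the programme during the wait has no start date. Read literally, that patient has no T1–T8 calendar and no total. The deviation form in Co-interventions and compliance is completed at discharge and has no option for never having started. The 15 % allowance in Sample size covers follow-up loss and programme extension only.
2. If one arm waits longer, its window opens later on the recovery curve, and it collects fewer sick-leave days with no treatment effect. A longer wait in the 40-h arm would favour non-inferiority; a longer wait in the 100-h arm would work against it.
3. Costs and QALYs in the cost-utility analysis do not cover the same months.

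At stake is one of the two analyses that carry the primary claim. The Strengths and limitations section itself expects unblinded patients, especially in the 40-h arm, to react to what they do not receive, so arm-related refusal is foreseeable, though not shown.

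**Working it through.** **The plan's own figures.** The window is 3.5 + 12 = 15.5 months, with 107 days expected in the 100-h arm. The log-scale margin reproduces: 30/107 = 28 %. The sample size of 174 also reproduces, if the ICC of 0.05 is taken as a factor of 1.05 (an assumption, as no formula is given): 69.57 × 1.05 rounds up to 74 per arm, and 148/0.85 = 174.1. It does not depend on where the window starts if SD, margin and expected difference are kept.

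**Order of the dates.** T0 → consent → open allocation → booking → start → T1 (+7 weeks) → T2 (+14 weeks) → T3–T8. The 1.5 months separates T0 from the start. Allocation lies between them, and later still when consent comes back by post, so the allocation-to-start gap is at most about 1.5 months and is not stated.

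**Effect of unequal waits.** Assume the share of working days lost falls as s(t) = s∞ + (s0 − s∞)·exp(−t/τ), with 21.75 working days a month. Solve τ so that 21.75 × ∫ s(t) dt over 0 to 15.5 months equals 107. Then open the window 2 or 4 weeks later, at the same length, and take the fall in the total. The curve shape, s0, s∞ and the extra wait are all assumptions; only 107 and 15.5 come from the article.

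| s0 | s∞ | τ (months) | 2 weeks later | 4 weeks later |
|---|---|---|---|---|
| 0.60 | 0 | 10.73 | 4.5 days | 8.8 days |
| 0.60 | 0.25 | 3.00 | 3.2 | 6.0 |
| 0.70 | 0 | 8.32 | 5.8 | 11.2 |
| 0.70 | 0.25 | 2.32 | 4.1 | 7.4 |
| 0.80 | 0 | 6.87 | 6.9 | 13.4 |
| 0.80 | 0.25 | 1.90 | 4.9 | 8.7 |

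The ranges are 3.2–6.9 days (11–23 % of the 30-day margin) and 6.0–13.4 days (20–45 %). The expected true difference in Sample size is 8 days. With equal waits the shift is zero.

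**Effect of losing non-starters.** If an excess share f of one arm never starts and is left out, and these patients differ from starters by D days, the difference moves by f × D. With f = 5–15 % and D = 25–100 days (both assumed), this is 0.05 × 25 = 1.25 to 0.15 × 100 = 15 days. If 5 % of both arms were lost on top of the 15 %, power would fall from 80.5 % to 78.1 %, so the issue is bias rather than power.

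**Cost-utility windows.** Fourteen weeks is 3.2 months. QALYs cover about 1.5 + 3.2 + 12 = 16.7 months; sick leave covers 3.2 + 12 = 15.2 months (15.5 in the article's rounding). The gap is about 1.5 months.

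**The case against.** A reader might infer that non-starters have no outcome and that the intention-to-treat test cannot include them. The article does not say so. It declares intention-to-treat, plans multiple imputation, and sends web questionnaires by e-mail with telephone chasing, so delivery does not depend on attendance. A first appointment is made after randomisation, so a planned start date will usually exist, and since T2 is set at 14 weeks after the start, T1–T8 could be run from it. The defect is an anchor undefined for these patients, not a stated exclusion.

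A reader might also infer a delay of 1.5 months after allocation, or start dates set separately by arm. Neither is supported. The delay is counted from baseline, one booking process is described for everyone, both programmes run at every centre, and allocation is blocked within centre. With equal waits on average, the start-anchored total is not biased by waiting, and the QALY mismatch affects both arms alike.

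Finally, a condensed article may leave the handling of non-starters to the full protocol or analysis plan. That excuses the missing rule, but not the time origin, which the article fixes explicitly and after randomisation. Imputation alone does not settle it either: a total counted from a start that never happened needs a definition before it can be imputed.

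**Conclusion.** The point holds in limited form. The document places time zero for the primary outcome, and the dates of T1–T8, at events after open randomisation, while requiring an intention-to-treat result for the non-inferiority claim. Followed literally, this leaves a non-starter without a defined window and allows waiting time and selection after allocation into the tested difference.

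The size is conditional. About 3–7 days for a 2-week and 6–13 days for a 4-week arm difference in waiting rest on an assumed recovery curve and on a difference that no passage reports; the 1.25–15 days for non-start rest on assumed rates. The documents do not show that bias will occur or that the intention-to-treat analysis fails. The difference of about 1.5 months between the QALY and absenteeism windows needs no assumption beyond the article's own delay figure. The change should be made because the exposure is avoidable at modest cost and because questionnaires not sent to non-starters cannot be recovered at the analysis stage.

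**What to change.** Set one time zero for every randomised patient: either randomisation, or the scheduled first-session date, recorded for all including those who never attend. Send T1–T8 on that calendar whether or not treatment starts or stops. State that the intention-to-treat analysis includes everyone randomised, and report waiting time and non-start by arm. Use the same window for costs and QALYs; absenteeism, health care usage and quality of life all have T0 data. Keep the total from actual start as a supporting analysis.

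**Cost of choosing randomisation.** Sick leave during the wait must be interpolated between T0 and T1, and variance rises slightly. The 107 days and the 28 % must be restated. As an illustration, a full 1.5 months at an assumed 60–80 % of working days lost adds 0.6 × 21.75 × 1.5 = 19.6 to 0.8 × 21.75 × 1.5 = 26.1 days, giving about 127–133 expected days. If 30 days is kept, the log-scale margin becomes 30/126.6 = 24 % to 30/133.1 = 23 %.

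**Cost of choosing the scheduled date.** The 15.5-month figures can stay, but any arm difference in scheduling remains and must be reported. A patient who declines before booking still needs a date.

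Either choice needs an amendment. Enrolment began in November 2014, so it changes the primary outcome definition during the trial and should be fixed while the analyst is still blinded.
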